##### Medication use

Participants will be advised to continue with their usual medication during the trial. However, the medication for knee OA should be discontinued 1 week before the next outpatient follow-up. All data about medications, particularly those for knee OA, including dose and frequency, will be recorded in the case report form by the physiotherapist at baseline and follow-up visits. Other cointerventions will be recorded in the self-report questionnaire.

### Sample size calculation

The sample size was calculated based on average overall knee pain (VAS) and physical function in daily life (WOMAC). The minimal clinically important difference to be detected in knee OA is a change of 18 mm on the 100-mm VAS for knee pain [3] and six units for physical function in WOMAC [45]. Therefore, according to a relevant literature [24], the standard deviations (SD) of clinical change are estimated to be 30 mm for knee pain and 12 units for physical function. Meanwhile, to achieve an effect size of at least 0.5 between groups in either pain or function in a two-armed clinical trial with a power of 80% and a significance level at 0.05 (α error), each group will require 51 participants [46]. To allow for a dropout rate of 10% [47, 48], 57 participants in each group and a total of 114 participants will be recruited by the orthopedic outpatient department.

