### Randomization allocation concealment

Patients will be recruited in strict accordance with the inclusion and exclusion criteria and will be subsequently randomized into the experimental group (leg swing exercise) or the control group (quadriceps strengthening exercise) at a ratio of 1:1. Specifically, an independent researcher who is not a part of the trial will generate 114 unique seven-digit codes using the random number function in the SAS software version 9.4 (SAS Institute Inc., Cary, NC, USA). Then these codes will be randomized into two groups and will be placed in a sealed, sequentially numbered, opaque envelope [22]. The envelopes will be stored securely. The recruited participants will be assigned to either the experimental or control group by extracting codes from the envelopes.

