### Statistical analysis

SPSS Statistics 24.0 software (IBM SPSS Inc., Armonk, New York) will be used for all statistical analyses performed by statisticians blinded to the clinical trial. Descriptive data and baseline and follow-up outcome measures will be presented as mean values (standard deviations) for continuous variables, and counts (percentages) for categorical variables. To manage missing data, we will perform a modified intention-to-treat analysis to include all participants. We will test for a difference between the two treatment arms at each time point (12 weeks and 24 weeks). The primary outcomes will be analyzed using mixed-design repeated measures analysis of variance for inter/intra-group differences. Bonferroni’s post hoc test will be applied if there is a significant result. A similar approach will be used to test the secondary outcomes. Non-parametric statistical tests will be used for any data that do not conform to a normal distribution. Categorical variables will be examined using the logistic regression test. To manage the false discovery rate (FDR), the methodology described by Benjamini and Hochberg will be adopted [49]. An FDR-adjusted *p* value of < 0.05 is considered statistically significant.

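### With 51 per group, a two-sided test has about 71% power for WOMAC function, not the stated 80%; the sample size paragraph does not say whether its test is one- or two-sided

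*Protocol article*

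**What the plan says.** All the inputs are in the protocol article under *Sample size calculation*. The target differences are "a change of 18 mm on the 100-mm VAS for knee pain [3] and six units for physical function in WOMAC", and "the standard deviations (SD) of clinical change are estimated to be 30 mm for knee pain and 12 units for physical function". The aim is "to achieve an effect size of at least 0.5 between groups in either pain or function", and the result is that "with a power of 80% and a significance level at 0.05 (α error), each group will require 51 participants". An allowance of 10% for dropout then gives 57 per group and 114 in total. Allocation is 1:1 (*Randomization allocation concealment*).

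Under *Statistical analysis* the plan is: "We will test for a difference between the two treatment arms at each time point (12 weeks and 24 weeks". The primary outcomes go through a mixed-design repeated measures ANOVA, with Bonferroni post hoc tests after a significant result and a Benjamini-Hochberg adjusted threshold of 0.05. Neither section says one-sided or two-sided. The hypothesis at the end of *Background* is worded in one direction, expecting leg swing exercise to do better.

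**The concern.** A bare 5% level next to ANOVA F tests and a test for a difference is ordinarily read as two-sided. On that reading the usual two-sample formula does not return 51 at an effect size of 0.5. The sample size and the analysis would then rest on different error rates, and the quoted 80% would not apply to the test actually run.

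The weak spot is WOMAC function, one of the two primary outcomes, because its target sits exactly at 0.5. If the paragraph stays as it is, a non-significant result on function will be read as coming from a trial with a 20% chance of missing a six-unit difference, when that chance is nearer 29%.

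**Working it through.** **Inputs** (all from *Sample size calculation*): differences of 18 mm and 6 units; SDs of change of 30 mm and 12 units; α = 0.05; power 80%; 51 per group; dropout 10%.

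**1. Effect sizes.** Function: 6/12 = 0.50. Pain: 18/30 = 0.60. The smaller matches the stated target of at least 0.5.

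**2. Reproducing the plan's 51.** The normal approximation is n per group = 2(z_α + z_0.80)²/d², where z_α is 1.960 (two-sided) or 1.645 (one-sided) and z_0.80 = 0.842. The noncentral t calculation refines it.

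| d | Test at 5% | Normal formula | Noncentral t |
|---|---|---|---|
| 0.5 | one-sided | 2(2.487)²/0.25 = 49.5 → 50 | 50.15 → **51** |
| 0.5 | two-sided | 2(2.802)²/0.25 = 62.8 → 63 | 63.77 → **64** |
| 0.6 | one-sided | 34.3 → 35 | 35.04 → 36 |
| 0.6 | two-sided | 43.6 → 44 | 44.59 → 45 |

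Of the four t-based results, only the one-sided test at 0.5 gives 51.

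**3. Dropout.** 51/0.90 = 56.7, so 57 per group and 114 in total. This step is right, and it confirms that 51 is the evaluable number per group.

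**4. Power of a two-sided 5% t test.** The noncentrality parameter is d√(n/2). With 51 per group there are 100 degrees of freedom and the critical value is 1.984.

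- Function, n = 51: 0.5 × √25.5 = 2.525, power 70.6%.
- Function, n = 57 (no dropout): 0.5 × √28.5 = 2.669, power 75.4%.
- Pain, n = 51: 0.6 × √25.5 = 3.030, power 85.1%.
- For comparison, function with n = 51 and a one-sided 5% test (critical value 1.660): power 80.6%, which is the plan's 80%.

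**5. Detectable effect.** With 51 per group and a two-sided 5% test, 80% power is reached at d = 0.560. That is 0.560 × 12 = 6.7 WOMAC units, or 0.560 × 30 = 16.8 mm. The first lies above the plan's own six-unit target for function. The second lies below its 18 mm target for pain.

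**The case against.** **The origin of 51 is not documented.** This stands. The paragraph cites a reference for its method that is not available here, and the hypothesis in *Background* is directional. A reader might conclude that the authors chose a one-sided test. The exact match makes a one-sided calculation the likeliest source, but the text does not show it, and *Statistical analysis* does not turn the directional hypothesis into a one-sided test.

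**Other two-sided routes reach about 51.** Averaging the two follow-up visits with a correlation near 0.6 does so: 63 × (1 + 0.6)/2 = 50.4. So does adjusting for a baseline value correlated at about 0.44: 63 × (1 − 0.44²) = 50.8. Both need a correlation that the paragraph does not give, so neither rescues the stated figure.

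**The word *either* may mean power to detect at least one outcome.** With effects of 0.5 and 0.6, each tested two-sided at 0.05 with 51 per group, the chance of at least one significant result is about 87% to 96% for assumed correlations of 0.9 down to 0. If both effects are 0.5, it is 77% to 92%. On that reading 80% is met or nearly met. But the paragraph describes no such calculation, correlation or multiplicity allowance. What does stand is that the shortfall should not be extended to pain at its own target, where power is about 85%.

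**A reader might infer that power is lower still because α is shared over two outcomes and two time points.** The documents do not support that. Benjamini-Hochberg is a step-up procedure and not an equal split: with two hypotheses, it rejects both at 0.05 when both p values are below 0.05. Bonferroni appears only as a post hoc test. Simulating Benjamini-Hochberg over the two primary outcomes at one visit leaves about 70% for function and a little over 80% for pain. The article does not define the full family of tests, so the loss could differ from this.

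**Conclusion.** The point holds for function. The stated 80% does not agree with the stated inputs under the non-directional tests that are planned. Two-sided power at the six-unit target is about 71% with 51 evaluable per group and 75% with all 57. Pain at 18 mm has about 85% and is adequately powered, but if its true effect were only 0.5 SD (15 mm) it would share function's 71%.

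These figures assume a two-sample comparison of change scores at one visit, the protocol's own SDs, a two-sided 5% test, and no false discovery rate adjustment. They do not depend on how 51 was obtained. That it came from a one-sided calculation remains an inference. The paragraph needs correcting in any case, because it leaves open whether the test is one- or two-sided, and the figure depends on it.

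**What to change.** Keep the total at 114; *Trial status* shows recruitment due to end in April 2022. In *Sample size calculation*, make these changes:

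- State that the comparison is two-sided at 5%, in line with *Statistical analysis*.
- Replace the 80% claim with two-sided power at 51 evaluable per group: about 71% for WOMAC function (6 units, SD 12) and about 85% for pain (18 mm, SD 30).
- Give the effect detectable with 80% power: 0.56 SD, about 6.7 WOMAC units or 16.8 mm.
- Note that these figures are before false discovery rate adjustment.

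Power gains from a baseline-adjusted model should not be brought into this correction. They would rest on an assumed correlation and on an analysis that the article does not name.

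The cost is wording only. No participants are added and no analysis changes, but the stated power for function becomes less favourable.

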### Statistical analysis

SPSS Statistics 24.0 software (IBM SPSS Inc., Armonk, New York) will be used for all statistical analyses performed by statisticians blinded to the clinical trial. Descriptive data and baseline and follow-up outcome measures will be presented as mean values (standard deviations) for continuous variables, and counts (percentages) for categorical variables. To manage missing data, we will perform a modified intention-to-treat analysis to include all participants. We will test for a difference between the two treatment arms at each time point (12 weeks and 24 weeks). The primary outcomes will be analyzed using mixed-design repeated measures analysis of variance for inter/intra-group differences. Bonferroni’s post hoc test will be applied if there is a significant result. A similar approach will be used to test the secondary outcomes. Non-parametric statistical tests will be used for any data that do not conform to a normal distribution. Categorical variables will be examined using the logistic regression test. To manage the false discovery rate (FDR), the methodology described by Benjamini and Hochberg will be adopted [49]. An FDR-adjusted *p* value of < 0.05 is considered statistically significant.

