In fact, there is another type of traditional Chinese exercise referred to as Daoyin, which is easier and is less cognitively demanding [11]. Although each of these exercises has its own training characteristics, they have common features. In general, Daoyin integrates both static and dynamic exercises with a great emphasis on regulating, breathing, and exercising intrinsic control and mental intent [12].

This study focused on leg swing exercise, which is an extremely important part of Daoyin based on the traditional Chinese medicine theory. This exercise is selected and recommended for three reasons. First, compared with T’ai chi and Baduanjin, the leg swing exercise of Daoyin focuses more on comprehensive training of the lower limb. This exercise is a combination of elements including strength training, active range of motion exercise, and aerobic activity. Second, since patients with knee OA have lower isokinetic strength in the hip muscles than healthy people, strengthening the muscles surrounding the hip joint may decrease pain [13, 14]. Leg swing exercise focuses on the joints of the lower limb including hip and knee joints. Third, as this clinical study will include mostly elderly participants, the exercise program should be simple enough for them to learn so that adherence will be good.

This clinical study aims to identify whether leg swing exercise, which is a type of Chinese traditional exercise, can relieve pain and improve physical function among patients with knee OA. Moreover, it wants to compare the efficacy of two different exercise programs on different outcomes such as knee pain, physical performance, health-related quality of life, patient-perceived satisfactory improvement, and lower limb muscle strength. We hypothesized that participants who take leg swing exercise will have greater improvements in pain intensity and physical function than those who take quadriceps strengthening exercise at 12 and 24 weeks after starting the intervention.

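### The primary ANOVA names no baseline covariate and opens post hoc tests on an unspecified significant effect; a baseline-adjusted arm comparison at weeks 12 and 24 would be clearer and generally more powerful

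*Protocol article*

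**What the plan says.** The hypothesis (protocol article, Background) is that leg swing participants "will have greater improvements in pain intensity and physical function than those who take quadriceps strengthening exercise at 12 and 24 weeks". It is about improvement, compared between arms, at two visits.

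Under Statistical analysis the plan first promises a test between the arms at each of weeks 12 and 24. It then names the model: "The primary outcomes will be analyzed using mixed-design repeated measures analysis of variance for inter/intra-group differences". A Bonferroni "post hoc test will be applied if there is a significant result". For awkward distributions it adds: "Non-parametric statistical tests will be used for any data that do not conform to a normal distribution". A Benjamini-Hochberg adjustment follows.

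The section does not say which ANOVA effect is the significant result, how the visit-wise tests relate to the ANOVA, or whether baseline is a level of the time factor. It names no covariate. Table 1 shows both primary outcomes measured at baseline, week 12 and week 24.

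**The concern.** A mixed-design ANOVA with one between-subject and one within-subject factor gives three F tests: group, time and group by time. They answer different questions, and the plan moves on after any of them.

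Both arms receive active exercise, and Study design calls the control the established intervention, so improvement in both is expected. A time effect would then open the post hoc tests while saying nothing about leg swing against quadriceps exercise. The group effect, if baseline is one of the averaged levels, mixes in a visit at which randomised arms do not differ on average.

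The baseline score also goes unused as a covariate, although adjusting for it is valid under randomisation and, apart from one degree of freedom, never less precise than the change score. Finally, a data-driven move to unnamed rank tests could leave the primary result without a mean difference in mm or WOMAC units, the scale on which Sample size calculation defines importance.

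**Working it through.** **Inputs from Sample size calculation.** Differences to detect: "a change of 18 mm on the 100-mm VAS for knee pain [3] and six units for physical function in WOMAC". Spread: "the standard deviations (SD) of clinical change are estimated to be 30 mm for knee pain and 12 units for physical function". So d = 18/30 = 0.6 for pain and 6/12 = 0.5 for function. The section plans "to achieve an effect size of at least 0.5 between groups in either pain or function", with 80% power, alpha 0.05, 51 per group and 10% dropout. Function is the binding outcome and is used below.

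**The plan's own figure.** A two-sample t test at d = 0.5 and 80% power needs 50.15, so 51 per group, with one-sided 0.05. Two-sided 0.05 needs 63.8, so 64. Then 51/0.9 = 56.7, so 57. The stated 51 is thus reproduced one-sided only. That is a separate matter, but two-sided power at 51 is 71%, which is the reference here.

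**Assumptions.** Equal variances and one common correlation ρ between visits. The document gives no ρ, so 0.3, 0.5 and 0.7 are shown. With an SD of change of 12, σ² = 144/[2(1−ρ)] = 102.9, 144 and 240. Baseline is taken as a level of time, with a 6-unit effect at both follow-ups, 51 per arm and two-sided 0.05.

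1. **Group effect.** The contrast is (0 + 6 + 6)/3 = 4 units, a loss of one third. Variance = (2/51)·σ²(1+2ρ)/3 = 2.15, 3.76, 7.53. Noncentrality = 16/variance = 7.44, 4.25, 2.13, tested on F(1,100).
2. **Interaction.** The deviations −4, 2, 2 have sum of squares 24. Noncentrality = (51/2)·24/[σ²(1−ρ)] = 612/72 = 8.5 at every ρ, on F(2,200).
3. **Change score at one visit.** Variance = 2·144/51 = 5.65. Noncentrality = 36/5.65 = 6.375, on F(1,100).
4. **Baseline-adjusted (ANCOVA) at one visit.** Variance = 5.65·(1+ρ)/2 = 3.67, 4.24, 4.80. Noncentrality = 9.81, 8.5, 7.5, on F(1,99).

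| Power | ρ 0.3 | ρ 0.5 | ρ 0.7 |
|---|---|---|---|
| Group effect | 77% | 53% | 30% |
| Interaction | 74% | 74% | 74% |
| Change score, one visit | 71% | 71% | 71% |
| ANCOVA, one visit | 87% | 82% | 77% |

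Unrounded, ANCOVA exceeds the interaction by 0.873 − 0.738 = 0.135 at ρ 0.3 and by 0.774 − 0.738 = 0.036 at ρ 0.7.

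**Alpha split over two visits.** At 0.025 per visit, ANCOVA has 80/74/68% at one visit. The change score (same noncentrality, 6.375) has 60%. Power to succeed with ANCOVA at one or both visits, if the effect lasts, is about 88% at ρ 0.5.

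**The gate.** In 8,000 simulated trials at each ρ, both arms improved by 0.5 SD of change with no difference between them. The time effect was significant in about 100%; the group and interaction tests stayed near 5%.

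**Fading effect, ρ 0.5.** If the week-12 effect halves by week 24, power is 33% for the group effect and about 60% for the interaction. If it is gone, 18% and 74%.

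**The case against.** The strongest reply is that the plan already promises the right comparison. The sentence just before the ANOVA commits to a between-arm test at weeks 12 and 24, and the interaction tests the hypothesis of greater improvement. A reader might infer that the analysis misses the treatment effect altogether. The document does not support that. The description fits the time effect and, through dilution, the group effect, but neither the interaction nor the visit-wise tests.

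Three further objections stand:

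- Baseline as a level of time is inferred from the wording on intra-group differences and the three-visit schedule. Figures for the three F tests depend on it.
- A reader might conclude that a fading week-12 benefit would be missed. That follows only if the group effect decides, and nothing says it does. The interaction keeps 74% power when the effect has vanished by week 24. Nor does an opened gate give a positive finding: the post hoc contrast must still pass its own adjustment.
- A reader might say that the non-parametric tests discard baseline and the repeated structure. No test is named, so that is conjecture.

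It can also be said that the deciding F test and covariates belong in an analysis plan. That covers silence, but this article goes further: it names a model and a gate, and the gate as worded admits an effect unrelated to treatment. Making week 12 the only primary visit would be a preference, since the hypothesis names both visits.

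**Conclusion.** The point holds in a limited form. The plan fixes a primary model with no stated baseline adjustment, leaves the deciding effect unnamed, and does not connect its visit-wise arm comparisons to that model. If time counts as the significant result, the gate is uninformative. If group counts, power at a lasting 6-unit effect is about 77% to 30% over ρ 0.3 to 0.7. If the interaction counts, the question is properly addressed at about 74% power, but without a visit-specific estimate.

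Against the change score, baseline adjustment raises one-visit power from about 71% to between 77% and 87%. Against the interaction the gain is about 4 to 14 points when one visit is tested at 0.05. With 0.025 per visit, single-visit power runs from 6 points above the interaction to 6 below it.

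All of this rests on an assumed ρ, on 12 units being the SD of change as the protocol states, on equal variances and correlations, and, for the three F tests, on baseline being a level of time. The size of the gain is therefore uncertain. That adjustment is at least as efficient as the change score, apart from one degree of freedom, does not depend on ρ.

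**What to change.** In Statistical analysis, define the primary analysis of each primary outcome as the between-arm mean difference at weeks 12 and 24, with 95% confidence intervals, from one model with the baseline score as covariate. This can be ANCOVA, or a mixed model with group-by-visit terms. Apply the stated multiplicity adjustment directly to these contrasts, and delete the step that waits for an unspecified significant result.

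Keep this model as primary when data look non-normal. Check residuals and use robust or bootstrap standard errors where needed, so that the estimate stays in mm and WOMAC units. Rank tests can serve as sensitivity analyses.

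The cost is analysis wording only. Baseline values of both primary outcomes are already collected, and no visit, measurement or participant is added.

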### Participants

In total, 114 patients aged ≥ 50 years with painful knee OA will be recruited from the orthopedic outpatient department of Shanghai Jiao Tong University Affiliated Sixth People’s Hospital.

The inclusion criteria will be as follows:
Patients aged ≥ 50 years oldThose with OA in at least one knee according to the American College of Rheumatology Classification Criteria [18]Those with knee pain on most days of the last monthThose presenting with knee pain for at least 3 monthsThose reporting a minimum average overall knee pain intensity of 40 on a 100-mm visual analog score (VAS) for most days in the last month [19]Those with a Kellgren-Lawrence grade (K-L grade) of 2–4 for knee OAThose willing to follow the physiotherapist’s recommendation for exercise trainingThose with smartphones downloaded with the WeChat app who are willing to receive text message reminders and send feedback to the physiotherapist during the trial.

Knee OA will be further confirmed via physical examinations in the orthopedic outpatient department and a full-length lower limb radiography will be performed in the hospital.

The exclusion criteria will be as follows:
Patients with knee joint injection within the last 6 months or planned surgery in the next 12 monthsThose who have taken oral corticosteroids within the last month or who received intra-articular corticosteroid injection within the last 3 monthsThose with systemic arthritic conditionsThose with previous knee fracture or malignancyThose with a previous history of hip or knee joint replacement, tibial osteotomy, or other surgeries of the hip or knee jointThose with any other neurological, muscular, or joint diseases that may currently affect the physical function of the lower limbThose who have participated in hip or knee muscle strengthening programs within the last 3 monthsThose without independent mobilityThose who reject the leg swing exercise or those who do not provide informed consent.

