### Blinding

Considering that most participants may have learned before the clinical trial that quadriceps strengthening exercise is a treatment for knee OA and that the group allocation can be revealed based on the interventional exercises, the participants will not be blinded to the treatment [16]. However, they will be blinded to the study hypotheses. As questionnaire-based outcomes are self-reported and participants are not blinded to treatments, the assessors of questionnaires will not be blinded. Since the physical performance tests are held in other enclosed rooms, assessors who collect physical function outcomes will be blinded. Statisticians who perform statistical analyses will be blinded. If there will be any unexpected adverse event caused by the exercise program, randomization allocation can be immediately unblinded by the study oversight committee.

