##### Overall knee pain

The average overall knee pain intensity in the last week will be self-reported by participants using the 100-mm VAS, with terminal descriptors of “no pain” (score 0) and “worst pain imaginable” (score 10) [19].

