##### Physical function

The WOMAC Osteoarthritis Index (Likert version 3.1) [28] will be used to assess the physical function of participants in daily life within the last week. This index is a self-reported, disease-specific instrument with high reliability, validity, and responsiveness [29]. The daily physical function subscale contains 17 questions, which include most physical activities in social life. These questions are with Likert response options ranging from “no problems” (score 0) to “extreme problems” (score 4), and the total score ranges from 0 to 68, with higher scores indicating worse physical function. The WOMAC physical function subscale has been included in the Knee injury and Osteoarthritis Outcome Score (KOOS) [30, 31] questionnaire.

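### The non-parametric fallback covers both primary outcomes, so the observed data could change the primary method and what it estimates

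*Protocol article*

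**What the plan says.** All of this is in the protocol article.

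- Statistical analysis, primary method: "The primary outcomes will be analyzed using mixed-design repeated measures analysis of variance for inter/intra-group differences". The arms are to be compared at 12 and at 24 weeks, secondary outcomes get a similar approach, and p-values are adjusted for the false discovery rate.
- Statistical analysis, fallback: "Non-parametric statistical tests will be used for any data that do not conform to a normal distribution". The section gives no criterion for non-normality. It does not say whether raw scores, changes or residuals are judged, and it names no replacement test.
- Overall knee pain: "The average overall knee pain intensity in the last week will be self-reported by participants using the 100-mm VAS".
- Physical function: for the WOMAC subscale, "the total score ranges from 0 to 68, with higher scores indicating worse physical function".
- Sample size calculation: the differences to detect are 18 mm (SD 30 mm) and 6 units (SD 12 units), with an effect size of at least 0.5, 51 per group, and 57 per group (114 in total) after 10% dropout.
- Participants: entry requires a "minimum average overall knee pain intensity of 40 on a 100-mm visual analog score (VAS) for most days in the last month".
- Blinding: "Statisticians who perform statistical analyses will be blinded".

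**The concern.** The fallback is a standing instruction, worded without exception, that overrides the named primary method according to what the data look like. Three things are at stake.

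- **The estimand.** The trial is sized on mean differences in mm and WOMAC units. A Mann-Whitney test at a visit asks whether scores in one arm tend to exceed those in the other, which is a different question.
- **The structure.** Standard rank tests work visit by visit or within an arm. They have no group-by-time term, which the mixed-design ANOVA does have.
- **Consistency.** Pain could be analysed one way and function another, or week 12 one way and week 24 another. The false discovery rate step would then pool p-values that answer different questions.

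**Working it through.** **1. What the sample size rests on.** The effect sizes are 18/30 = 0.6 for pain and 6/12 = 0.5 for function. At 0.5, 80% power and one-sided alpha 0.05, the normal approximation gives 2 × (1.645 + 0.842)² / 0.5² = 49.5, so 50 per group. The t-test gives 51, the plan's figure. Then 51/0.9 = 56.7, so 57 per group and 114 in total. (A two-sided alpha of 0.05 needs 63 to 64 per group. The article does not state sidedness, and that is a separate matter.) The calculation is for a comparison of means.

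**2. What a mean-based analysis reports.** With 51 per arm and the plan's SDs, the standard error of a difference in mean change is SD × √(2/51) = SD × 0.198.

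- Pain: 30 × 0.198 = 5.9 mm, an approximate 95% interval of ± 11.6 mm, to be read against 18 mm.
- Function: 12 × 0.198 = 2.4 units, about ± 4.7 units, to be read against 6 units.

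A rank p-value offers no counterpart on these terms. At this size the sampling distribution of a mean difference on a bounded scale is close to normal even when the scores are not.

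**3. Could the rule be triggered?** Suppose normality is tested at 0.05 in each arm, for two primaries at two follow-up visits: 2 × 2 × 2 = 8 checks. If the checks were independent and the data exactly normal, at least one would fail with probability 1 − 0.95⁸ = 34%. Adding baseline makes 12 checks and 1 − 0.95¹² = 46%. Real checks are correlated, so these are upper-end figures. The choice of test and level is an assumption.

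**4. Does the 40-mm entry cut-off make it likely?** If baseline VAS is taken to be the truncated entry rating itself (normal, cut to 40–100, parent mean 50–60, SD 15–20), Shapiro-Wilk at 0.05 rejects in 68–99.7% of simulated samples of 114. That equates two ratings with different recall periods. A second simulation let them differ. It assumed parent mean 45–70, SD 15–20, entry-to-baseline correlation 0.6–1.0, 57 per arm, follow-up slope 0.5 on baseline, residual SD 22, and scores limited to 0–100.

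| Variable checked | Share of trials rejecting normality |
|---|---|
| Pooled baseline VAS, correlation 1.0 | 14–100% |
| Pooled baseline VAS, correlation 0.6–0.8 | 4–53% (at most 18% for means 45–65) |
| Change score, either arm | 6–23% (about 10% expected by chance) |
| 12-week score, either arm | 7–93% |
| Model residuals | 3–64% |

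The high values in the last two rows occur when the mean is low, and they come from the floor at 0. At mean 45 and SD 15, the 12-week rate falls from 93% to 87% to 80% as the correlation with the truncated entry score rises through 0.6, 0.8 and 1.0. If the cut-off were the cause, the rate should rise.

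**5. Does switching cost anything in error rates?** In one assumed scenario (51 per arm, 4,000 runs), testing normality first and then choosing the test gave type I error 0.049, against 0.047 for the t-test on change. Power was 0.79 for both at a 15-mm difference. This is a simple two-arm comparison, not the full ANOVA.

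**The case against.** The strongest reply is that a non-parametric fallback is a conventional sentence, declared in advance and applied by blinded statisticians, and that its criterion and replacement test belong in a statistical analysis plan that is not shown. Much of this stands. Blinding and advance declaration limit selective choice, and the missing criterion and test name are not the point here. The point is what the article does state: a rule that reaches the primary outcomes and lets their distribution decide the method. An analysis plan that followed this wording would inherit the problem.

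Means and SDs will also be reported for every outcome, so a difference in mm or units could still be read off. That is true, but it would have no matching test or interval.

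A reader might infer four stronger things that the documents do not support.

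- **That the 40-mm criterion will probably trigger the switch.** It is a last-month rating applied once, at entry. The outcome is a last-week rating compared at weeks 12 and 24, and WOMAC function has no cut-off.
- **That raw scores rather than residuals will be tested.** The article does not say which.
- **That the switch loses baseline adjustment and the handling of missing visits.** The planned ANOVA states no baseline covariate and conventionally needs complete cases, so the switch does not cause either loss.
- **That false positives rise or power falls.** The one scenario run shows neither.

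**Conclusion.** The point holds in a limited form. As worded, the fallback applies to both primary outcomes. The method and the estimand could therefore be set by the observed data and could differ between outcomes or visits, and the replacement would not deliver the mean difference on which the trial is sized. A switch is possible: up to 34–46% by chance alone under the independence assumption, and otherwise dependent on which variable is checked and how close scores lie to the floor. No probability can be fixed from the documents, because the parent means, SDs, correlations and normality test are all assumed. The harm is to the definition and interpretation of the primary result. Harm to type I error or power has not been demonstrated. The rule governs the primary outcomes and costs almost nothing to repair, so it should be changed before the data are analysed.

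**What to change.** Replace the fallback sentence with text to this effect:

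- For both primary outcomes the prespecified parametric repeated-measures analysis is kept whatever the distribution. The between-arm mean difference and its confidence interval are reported at weeks 12 and 24.
- If model residuals are markedly non-normal, bootstrap intervals for the same mean differences, or a rank-based analysis, are added as sensitivity analyses only.
- Rank methods are the main analysis only for ordinal or capped secondary measures named in advance, such as the one-leg stand capped at 30 s.

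This retains the planned ANOVA and needs no new primary model. The cost is a few sentences and a possible small loss of efficiency if outcomes are heavy-tailed. The 51, 57 and 114 are unaffected. The Trial status section shows recruitment still open at the protocol version of 6 March 2022, with 24-week follow-up to come, so at that date the change could precede the analysis.
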